### Outcomes

#### Primary outcome measure

The primary outcome measure will be the International Consultation on Incontinence Modular Questionnaire Urinary Incontinence short form (ICIQ-UIsf), which provides a brief and robust assessment of the impact of symptoms of urinary incontinence on quality of life and outcome of treatment and is scored on a scale from 0 (not) – 21 (severely affected). Previous research has examined the ICIQ-UIsf questionnaire and found it to have good reliability and constructive validity [14] and to correlate well with urodynamic findings [15]. This questionnaire is validated in the German language [16]. For measurement time points see Table 1.

**Table 1 Tab1:** Outcome measures and personal physiotherapy consultation time points

	Baseline before intervention phase	16-week intervention phase (1) after randomization into control group and experimental group									After intervention phase	6-month follow-up
Visits	1	2	3	4	5	6	7	8	9	10	11	12
Weeks	−1	1	2	4	6	8	10	12	14	16	16 + 1	16 + 26
Personal Physiotherapy Consultation (PT)		PT1	PT2	PT3	PT4	PT5	PT6	PT7	PT8	PT9		
Primary outcome												
ICIO-UIsf	x		x	x	x	x	x	x	x	x	x	
Secondary outcomes												
EMG (rest, MVC)	x										x	x
EMG (VFC, SJ, CMJ, DJ)	x										x	x
EMG (running 7, 9, 11 km/h)	x										x	x
ICIQ-UIsf												x
ICIQ-LUTSqol	x										x	x
20-min pad test	x										x	x
Tertiary outcomes												
Manual muscle testing	x										x	x
Therapy adherence			x	x	x	x	x	x	x	x	x	x

*ICIQ-UIsf* International Consultation on Incontinence Modular Questionnaire Urinary Incontinence (short form), *EMG* electromyography, *MVC* maximal voluntary contraction, *VFC* voluntary fast contraction, *SJ* squat jump, *CMJ* counter movement jump, *DJ* drop jump, *ICIQ-LUTSqol* International Consultation on Incontinence Modular Questionnaire Urinary Incontinence Symptoms Quality of Life

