#### Secondary and tertiary outcome measures

The secondary outcome measure will be the EMG activity of the PFM during rest, maximal voluntary contractions (MVCs), voluntary fast contractions (VFCs), and during involuntary contractions during squat jumps (SJs), counter movement jumps (CMJs), drop jumps (DJs), and treadmill running at 7, 9, and 11 km/h [17]. As there is a relation between high impact activities and SUI prevalence [18], those different and comprehensive test exercises will be chosen to represent typical situations of involuntary urine loss and different muscle action forms (isometric-concentric voluntary muscle actions: MVC, VFC; involuntary eccentric-concentric muscle actions: SJ, CMJ, DJ, running).

Additionally, the 20-min pad test [19, 20] and the International Consultation on Incontinence Modular Questionnaire Urinary Incontinence Symptoms Quality of Life (ICIQ-LUTSqol) [21] will be implemented as secondary outcomes. The pad test will provide information regarding the efficacy of the therapy protocols to the UI symptoms (such as changes in the leakage volume) and the ICIQ-LUTSqol evaluates the impact on the participant’s quality of life with reference to social effects. It consists of 20 questions, which lead to a summary score between 19 and 76 points (greater values indicate higher impact on quality of life) and is available in German [22].

As tertiary outcomes PFM strength will be digitally assessed according to the Oxford Grading Scale [23], and adherence to the home exercise program will be assessed, that is, how many of the total therapy sessions will be completed individually. The home exercise adherence data will be collected with a simple training diary questionnaire.

For measurement time points, see Table 1.

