**Fig. 1 Fig1:**
[figure not shown]
CONSORT study flow diagram

The outcomes of the control and experimental group will be analyzed by the repeated measures within-between interactions ANOVA approach and an intention-to-treat analysis (last observation carried forward method). No subgroup analyses are planned.

Primary analysis: For the descriptive analyses means, standard deviations, 95 % confidence intervals, and median, quartiles, minima, maxima will be used.

To compare the primary outcome ICIQ-UIsf between and within the two groups (control group, experimental group) at ten time points (before intervention, physiotherapy sessions 2–9, after intervention), ANOVA models for longitudinal data according to Brunner et al. [30] will be used. All statistical analyses will be realized after the final measurement of the last patient at the time point after intervention. The statistics will be calculated by SPSS and R software packages in the current versions. The repeated measure design with ten time points allows us to monitor how patients change over time, in both short-term (before/during intervention) and long-term situations (before/after intervention).

Secondary and tertiary analyses: All secondary and tertiary outcomes will be analyzed following the same approach and with the same statistical procedures as for primary outcomes. Generally, rational data will be checked for normality using Q-Q-plots. If the normality assumption is not violated, parametric ANOVA models for longitudinal data will be used [31]. As for intra-session retest procedures (EMG amplitude and frequency), data will also be described and checked for their reliability (ICC, SEM, MD, ANOVA).

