#### Intervention

Both therapy programs (control group, experimental group) are based on the latest position stand paper of the American College of Sports Medicine [11, 32], PFM motor learning concepts [33, 34], and strength training concepts [11, 12, 32, 35, 36]. The planned progression of training for strength, power, and hypertrophy [11, 32, 33, 35, 36] is shown in Table 2.

**Table 2 Tab2:** Time schedule and progression phases of training for motor learning, strength, hypertrophy, and power for experimental and control groups

Week	Experimental group	Control group	Training frequency
1–5	Motor learning + power	Motor learning	45 (plus 3 personal physiotherapy consultations)
6–9	Strength + hypertrophy + power	Strength + hypertrophy	12 (plus 2 personal physiotherapy consultations)
10–16	Power	Strength + hypertrophy + power	21 (plus 4 personal physiotherapy consultations)

Training procedures for motor learning, strength, hypertrophy, and power training phases follow the training principles of variation/periodization, muscle action and velocity of muscle action, loading, volume, exercise selection, rest period, and frequency [11, 12] for both groups. The training program will last 16 weeks and will contain 9 personal physiotherapy consultations and 78 home training sessions of approximately 15 minutes (weeks 1–5 3x/week, 3x/day; weeks 6–16 3x/week, 1x/day) (Tables 1 and 2). Motor learning and strength and hypertrophy phases are comparable for both groups. However, the main difference between the programs is the applied type of muscle action (control group: isometric, concentric; experimental group: isometric, concentric, eccentric und eccentric-concentric) and speed of movement (control group: voluntary slow to moderate (to explosive) [33, 35]; experimental group: explosive, reactive, reflexive). After completion of the 16-week training program, the participants will participate in no further personal physiotherapy consultations; however, they will continue home training sessions 3x/week until the 6-month follow-up. During the intervention period participants may continue with their individual activities of daily life.

The personal physiotherapy consultations will take place in the physiotherapy center of the Women’s Hospital, Bern University Hospital and University of Bern, Switzerland. The treating physiotherapists are all specialized and experienced in PFM rehabilitation.

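### Carrying the last observation forward does not suit diary-recorded adherence: on a per-visit count or rate, it credits sessions not done by women who stop and return no further diary

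*Protocol article*

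**What the plan says.** Under Statistical analyses, the protocol article says that the outcomes of both groups will be analysed by repeated-measures ANOVA and "an intention-to-treat analysis (last observation carried forward method". For the remaining outcomes it adds: "All secondary and tertiary outcomes will be analyzed following the same approach and with the same statistical procedures as for primary outcomes".

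Under Secondary and tertiary outcome measures, adherence to the home programme is a tertiary outcome, described as "how many of the total therapy sessions will be completed individually". Its source is also given: "The home exercise adherence data will be collected with a simple training diary questionnaire". Table 1 schedules the row "Therapy adherence" at visits 3 to 12, that is, at PT2 to PT9, after the intervention phase and at the 6-month follow-up.

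Under Intervention, the prescription is "78 home training sessions of approximately 15 minutes (weeks 1–5 3x/week, 3x/day; weeks 6–16 3x/week, 1x/day"). After week 16, "they will continue home training sessions 3x/week until the 6-month follow-up".

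Nothing in the article exempts adherence from the carry-forward rule. Nor does it say whether the value at each visit is cumulative or covers only the interval since the previous visit.

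**The concern.** For a symptom score, carry-forward replaces an unknown value with a guess. Adherence is different, because after a documented stop the number of later sessions is known to be zero. If that woman returns no further diary, the rule enters her earlier training level in place of the known zero.

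A second problem does not depend on whether she stopped. The prescribed number of sessions per interval falls during the programme, so an early count carried forward can exceed everything prescribed for the later interval.

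At stake is the adherence comparison. The last paragraph of the Background places therapy adherence within the secondary objective, and the Discussion expects the new programme to be well accepted by patients. If one programme were abandoned more often, an adherence analysis under this rule could show the arms as alike.

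**Working it through.** **Inputs from the protocol article**
- Prescribed home sessions: 9 per week in weeks 1–5 and 3 per week in weeks 6–16 (Intervention).
- Adherence visits in the intervention phase: weeks 2, 4, 6, 8, 10, 12, 14 and 16 (Table 1). I take each diary to run to the end of the visit week.
- Dropout: 10% (Sample size calculation).

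**Assumed inputs**
- Adherence per interval before stopping, *p* = 0.7 to 0.9, the same for women who stop and women who continue.
- All dropouts have stopped training and return no further diary.
- Stopping by arm, 5% against 15%, for illustration only.

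**1. The plan's own figure.** 5 × 9 + 11 × 3 = 45 + 33 = 78 sessions. This reproduces the stated total and agrees with Table 2 (45 + 12 + 21 = 78).

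**2. Sessions prescribed between adherence visits.** Weeks 1–2: 18. Weeks 3–4: 18. Weeks 5–6: 9 + 3 = 12. Each later two-week interval: 6. Sum: 18 + 18 + 12 + 5 × 6 = 78.

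**3. Fully adherent woman who stops and returns no further diary, by scale**

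| Scale | Stops after week 4 (36 of 78 done, 46%) | Stops after week 8 (54 of 78 done, 69%) |
|---|---|---|
| Count per interval | 18 carried into one interval prescribing 12 and five prescribing 6 | 6 carried into four intervals in which she did none |
| Rate per interval | 100% at every later visit; true rate 0% | 100% at every later visit; true rate 0% |
| Cumulative count | 36 at every later visit, correct | 54 at every later visit, correct |

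In the week-4 case, the carried count is above the prescription whether she stopped or kept training. At the 6-month visit, a carried two-week count fails in another way: 26 × 3 = 78 sessions are prescribed from week 17 to week 42, and a carried 6 would read as 6/78 = 8% even for a woman who trained throughout.

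**4. Effect on a group mean (rate per interval).** If a fraction *d* has stopped without further diaries, the late mean is *p* under carry-forward and *p*(1 − *d*) when stops are scored as zero. The overstatement is *p* × *d*.
- *d* = 10%: 0.7 × 0.10 = 7 points; 0.8 × 0.10 = 8 points; 0.9 × 0.10 = 9 points.
- *d* = 20% (assumed): 14 to 18 points.

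**5. Effect on the arm comparison.** With *p* = 0.8 and stopping of 5% against 15%, zero-scoring gives 0.8 × 0.95 = 76% against 0.8 × 0.85 = 68%, a difference of 8 points. Carry-forward gives 80% against 80%, a difference of 0.

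**The case against.** The strongest reply is that the harm depends on the scale. The article describes adherence in terms of completed sessions out of the total, which can be read as a running count against the programme. On that reading, carry-forward gives the right answer for a woman who stopped. This stands as a limit on the point, but the article does not fix that scale. A cumulative count would also undercount a woman who is lost to follow-up and still trains at home.

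A reader might infer more than the text supports, in four ways:
- *Every woman who stops keeps her earlier adherence.* Carry-forward fills only missing values. A woman who stops but still returns diaries has an observed zero or low value, and that value is used.
- *The value after dropout should always be zero.* It is known to be zero only after a documented stop. A woman lost to follow-up may still be training, and scoring her zero is an assumption that errs the other way.
- *Discontinuation is hidden.* The CONSORT flow described under Statistical analyses reports loss to follow-up and discontinued intervention. The masking is confined to the adherence comparison.
- *Adherence totals would exceed 100% of the programme.* Adding carried counts after a week-4 stop gives 8 × 18 = 144 against 78, but the article nowhere proposes adding them. What stands is that single carried values exceed the prescription.

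It can also be said that a condensed article leaves the scoring of missing diaries to the full protocol or analysis plan. That would answer a complaint about silence. Here the article states a rule that covers all tertiary outcomes, and the rule does not suit this one.

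**Conclusion.** The point holds in a limited form. As written, carry-forward reaches adherence. On a per-visit count or rate, it credits sessions not done by women who stop and return no further diary, and an early count can exceed what was later prescribed.

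The overstatement of late per-interval adherence is about 7–9 percentage points. This rests on the protocol's 10% dropout, on assumed prior adherence of 70–90%, and on the assumption that all dropouts have stopped training. It is smaller if some dropouts continue, and absent for stopped women if the measure is cumulative. The illustrated loss of an 8-point arm difference rests on stopping rates that the article does not give.

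Adherence is a tertiary outcome. The sample size was calculated for the ICIQ-UIsf, so neither it nor the primary comparison changes. The amendment is worth making but does not bear on the trial's main conclusion.

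**What to change.** Amend the sentence on secondary and tertiary analyses as follows:
- Exempt adherence from last observation carried forward.
- Report completed divided by prescribed sessions, separately for weeks 1–16 (78 prescribed) and for week 17 to the 6-month follow-up (3 per week as stated).
- Score sessions after a documented stop of training as zero.
- For women lost to follow-up or with unreturned diaries, treat adherence as missing and show a sensitivity range from no further sessions to continued training at the earlier rate.

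The cost is a few sentences in the analysis section. The only data needed are the diary and the date on which training stopped. The downside is that reported adherence will look somewhat less favourable.

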### Detailed study plan

#### Patient recruitment/consent procedure

Patients will be recruited from the urogynecology consultation of the Women’s Hospital, Bern University Hospital and University of Bern, Switzerland. All participants for the study will be provided a participant information sheet and a consent form describing the study and providing sufficient information for them to make an informed decision about their participation in the study.

Each participant will be specifically informed that the participation in the study is voluntary and that she may withdraw from the study at any time and that withdrawal of consent will not affect her subsequent medical assistance and treatment.

#### Allocation of patients

Patients with written informed consent are randomly allocated to one of the two therapy groups (control group, experimental group). The allocation sequence will be generated by the independent urogynecology secretariat using online randomization software (http://randomization.com); allocation ratio = 1:1 (control group:experimental group). The allocation will be concealed in sealed, opaque, sequentially numbered envelopes, which will be stored at the secretariat and can be opened one at a time for each eligible patient. Physiotherapists treating patients will be informed about enrollment and group allocation of their patient by the independent secretariat.

#### Outcome measurements

Baseline (before intervention phase), after intervention phase, and 6-month follow-up measurements (of primary, secondary, and tertiary outcomes) will take place at the Bern University of Applied Sciences movement laboratory by two experienced pelvic floor physical therapists, who are blinded regarding group allocation of participants. Measurements during the 16-week intervention phase (ICIQ-UIsf; primary outcome) will be taken by the treating physiotherapists. However, to guarantee blinding of the outcome, the participant will fill in the questionnaire in the absence of the treating physiotherapist and seal it in an envelope, which will be given to the outcome assessor.

#### Intervention

Both therapy programs (control group, experimental group) are based on the latest position stand paper of the American College of Sports Medicine [11, 32], PFM motor learning concepts [33, 34], and strength training concepts [11, 12, 32, 35, 36]. The planned progression of training for strength, power, and hypertrophy [11, 32, 33, 35, 36] is shown in Table 2.

**Table 2 Tab2:** Time schedule and progression phases of training for motor learning, strength, hypertrophy, and power for experimental and control groups

Week	Experimental group	Control group	Training frequency
1–5	Motor learning + power	Motor learning	45 (plus 3 personal physiotherapy consultations)
6–9	Strength + hypertrophy + power	Strength + hypertrophy	12 (plus 2 personal physiotherapy consultations)
10–16	Power	Strength + hypertrophy + power	21 (plus 4 personal physiotherapy consultations)

Training procedures for motor learning, strength, hypertrophy, and power training phases follow the training principles of variation/periodization, muscle action and velocity of muscle action, loading, volume, exercise selection, rest period, and frequency [11, 12] for both groups. The training program will last 16 weeks and will contain 9 personal physiotherapy consultations and 78 home training sessions of approximately 15 minutes (weeks 1–5 3x/week, 3x/day; weeks 6–16 3x/week, 1x/day) (Tables 1 and 2). Motor learning and strength and hypertrophy phases are comparable for both groups. However, the main difference between the programs is the applied type of muscle action (control group: isometric, concentric; experimental group: isometric, concentric, eccentric und eccentric-concentric) and speed of movement (control group: voluntary slow to moderate (to explosive) [33, 35]; experimental group: explosive, reactive, reflexive). After completion of the 16-week training program, the participants will participate in no further personal physiotherapy consultations; however, they will continue home training sessions 3x/week until the 6-month follow-up. During the intervention period participants may continue with their individual activities of daily life.

The personal physiotherapy consultations will take place in the physiotherapy center of the Women’s Hospital, Bern University Hospital and University of Bern, Switzerland. The treating physiotherapists are all specialized and experienced in PFM rehabilitation.

An additional document file presents the intervention (therapy plan of intervention group and control group) in detail [see Additional file 1].

#### Adverse events

In the current study there are no anticipated risks or inconveniences, as the applied intervention and examinations are well known and widely applied in pelvic floor standard physiotherapy. The additional exercises of the experimental group are also well known and applied in physiotherapy; however, they have not yet been used with SUI patients.

All the women are asked during every personal physiotherapy and measurement consultation whether they experience any adverse effects.

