#### Sample size calculation

Sample size calculation was performed with G*Power software [27], using the statistical model of an ANOVA approach (repeated measures, within-between interactions). To this day there is no comparable training study (RCT) to estimate sample size based on available data from ICIQ-UIsf. Consequently, sample size was estimated theoretically and an effect size of = 0.1, indicating a small effect [28] will be accepted. The sample size was calculated for the primary outcome ICIQ-UIsf with the following assumptions: α = 0.05, power (1–β error probability) = 0.8, number of groups = 2, number of measurements = 10; correlations among repeated measures were estimated conservatively low with 0.5. Based on these assumptions, a total sample size of N = 80 was estimated. In anticipation of dropouts (10 %: n = 8) or a violation of normality assumption (+10 %: +n = 8), a final sample size of N = 96 (48 participants per group) results.

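### The 25 weeks of home training between visits 11 and 12 are covered by one scheduled adverse-effect question, asked at the 6-month visit

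*Protocol article*

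**What the plan says.** The Adverse events section of the protocol article gives one scheduled procedure for eliciting harms: "All the women are asked during every personal physiotherapy and measurement consultation whether they experience any adverse effects". The same section expects no risks, on the ground that the procedures are familiar. It adds that the experimental group's additional exercises are known in physiotherapy generally; "however, they have not yet been used with SUI patients".

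The dates of the consultations are in Table 1. Physiotherapy consultations run from week 1 to week 16, and measurement consultations are at week −1, week 16 + 1 and week 16 + 26. For the period after week 16 the Intervention section states that "the participants will participate in no further personal physiotherapy consultations; however, they will continue home training sessions 3x/week until the 6-month follow-up".

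A home-training record already exists. Under Secondary and tertiary outcome measures: "The home exercise adherence data will be collected with a simple training diary questionnaire". Table 1 schedules adherence at visit 12 as well as during the intervention, so adherence data are planned for the follow-up period too.

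**The concern.** Questioning that follows the consultations works well while consultations are frequent. It becomes thin once they stop and training does not. For most of the follow-up the schedule contains no occasion on which a woman is asked about harm. What she reports at visit 12 then depends on what she remembers from nearly half a year. Strain, pain or a temporary worsening that came and went in that time is the kind of effect most easily lost.

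The stake is the safety description, not the efficacy result. Adverse effects are not a listed primary, secondary or tertiary outcome, and no planned efficacy comparison depends on them. But the article presents the added exercises as new to women with stress urinary incontinence, and both the Abstract and the Discussion foresee immediate use in practice if the programme succeeds. Readers will want this trial to say how well the exercises were tolerated, including when done at home without regular contact.

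**Working it through.** **Inputs**

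- Visit weeks (Table 1): −1, 1, 2, 4, 6, 8, 10, 12, 14, 16, 17 (16 + 1), 42 (16 + 26).
- Home sessions in the intervention phase (Intervention section): "The training program will last 16 weeks and will contain 9 personal physiotherapy consultations and 78 home training sessions of approximately 15 minutes", at 3 days a week with 3 sessions a day in weeks 1–5, and 3 days a week with 1 session a day in weeks 6–16.
- Home sessions afterwards (Abstract and Intervention section): 3 a week until the 6-month visit.

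**Step 1. Reproduce the plan's own figure.** Weeks 1–5: 5 × 3 × 3 = 45. Weeks 6–16: 11 × 3 × 1 = 33. Total 45 + 33 = 78. Table 2 gives 45 + 12 + 21 = 78. The stated figure reproduces.

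**Step 2. Intervals between scheduled questions.** Differences of successive visit weeks: 2, 1, 2, 2, 2, 2, 2, 2, 2, 1, 25. The longest interval up to visit 11 is 2 weeks. The last is 42 − 17 = 25 weeks, which is 25 / 2 = 12.5 times as long.

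**Step 3. Home sessions covered by one question.**

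| Period | Sessions per week | Longest interval | Sessions per question |
|---|---|---|---|
| Weeks 1–5 | 9 | 2 weeks | at most 2 × 9 = 18 |
| Weeks 6–16 | 3 | 2 weeks | 2 × 3 = 6 |
| Week 17 to week 42 | 3 | 25 weeks | 25 × 3 = 75 |

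**Step 4. Share of the whole programme.** Sessions after week 16: 26 × 3 = 78. Total: 78 + 78 = 156. Sessions between visits 11 and 12: 75. Share: 75 / 156 = 48%. (The other 78 − 75 = 3 follow-up sessions fall between week 16 and visit 11.)

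**Step 5. Distribution of the questions.** From visit 2 to visit 12 there are 11 scheduled occasions. Ten fall by week 17, and one covers the remaining 25 weeks.

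The documents give no recall or event rate, so the number of effects that would be missed cannot be computed. The size is therefore stated as the exposure covered by a single question.

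**The case against.** The strongest reply is that this is a two-sentence passage in a condensed article and contradicts nothing. It says when women are asked. It does not exclude spontaneous reports or diary notes, and procedures for unscheduled reporting commonly sit in the full protocol, which is not shown. Home sessions in weeks 1–16 are also done at home, so what changes after week 17 is the frequency of contact, not the setting. The article also does not list which exercises make up the follow-up training; the detailed therapy plan is in an additional file that is not shown.

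All of that stands, and it limits the point to scheduled elicitation. It does not remove the point: the visit weeks, the end of physiotherapy consultations and the continuing home training are all stated, so the 25-week interval does not rest on silence.

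Four stronger readings are tempting, and the documents do not support them.

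- **Adverse effects are collected only at consultations.** The article describes one scheduled route and does not call it the sole route. Likewise, the diary is described for adherence, without a statement that it holds nothing else.
- **Women who leave are never asked.** A woman who later leaves was asked at every consultation she attended. The Statistical analyses section lists stopping the intervention separately from loss to follow-up, and a woman who stops training may still attend visits 11 and 12. Whether those who leave altogether are contacted is not shown.
- **Some 8 to 10 women would lack adverse-effect data, biased in favour of the more harmful arm.** The 10% comes from the sample size allowance, "In anticipation of dropouts (10 %: n = 8) or a violation of normality assumption (+10 %: +n = 8), a final sample size of N = 96". It is a planning figure for the primary outcome, which ends at visit 11, and says nothing about when or why women leave. A bias by arm would need harm-related dropout that differs between arms, for which the article gives no evidence.
- **The present tense means that resolved events go uncounted.** The sentence summarises a procedure. The wording put to participants is not shown.

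**Conclusion.** The point holds as a weakness of design that is cheap to improve. Scheduled questioning goes from intervals of at most 2 weeks to one interval of 25 weeks, and about 75 of 156 scheduled home sessions (48%) are covered by a single recall question at visit 12. Transient adverse effects in that period are likely to be under-recorded.

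This rests on three assumptions: that Table 1 shows every scheduled contact; that women train at the stated frequency, so that 75 sessions is a scheduled and not an observed number; and that recall of minor effects fades over about six months, for which the documents give no figure. The relevance to the new exercises further assumes that the experimental group's follow-up training includes them. The primary analysis and the sample size are unaffected.

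**What to change.** 1. Add one line to the existing training diary, kept through the 6-month follow-up: date, complaint, and whether a session was missed or cut short because of it. Keep it to the complaint, without a description of the exercise, so that the entry does not reveal the arm to a blinded assessor.
2. At visits 11 and 12, ask about any adverse effect in the whole period since the previous visit.
3. Report adverse effects by arm, separately for the intervention phase and the follow-up.
4. Confirm whether women who discontinue are contacted about reasons and adverse effects. If they are, or if this is added, the blinded outcome assessors should make the contact. The secretariat should not, because it generates the allocation sequence and informs the physiotherapists of each woman's group (Allocation of patients section).

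The cost is one diary line, one reworded question and slightly more participant burden. Visits, training and the efficacy analysis do not change. Women already in the trial can receive the revised diary from the date of the change, and the report should state that date.
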